#### Primary outcome

The primary study outcome will be insomnia severity at post-intervention, assessed using the Insomnia Severity Index (ISI; [27]), a questionnaire that is commonly used in insomnia research [20, 29, 38] and clinical care [15]. Insomnia severity will be assessed at all measurement points (baseline, post-intervention 10 weeks after randomisation, and follow-up 6 months after randomisation). The ISI questionnaire consists of seven items, each answered on a 5-point Likert scale with response options ranging from 0 to 4 and a total score ranging from 0 to 28. In several studies, the ISI has demonstrated good internal consistency with *α* ranging from 0.70 to 0.90 [27, 28, 39]. For all measurement points, total scores will be calculated.

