### Sample size {14}

Since there is neither a validated non-inferiority margin for the insomnia treatment nor an established procedure for determining one, we followed the recommendation of the Delta2 group and considered different perspectives, including anchor-based clinical judgement and distribution-based reasoning to select the non-inferiority margin of the primary outcome (ISI) for this trial [58]. First, most clinicians involved in this trial agreed that new insomnia treatments are not inferior to the first-line treatment if the difference in post-intervention ISI scores is less than 2 points. Accordingly, 2 or more points were considered the minimally important difference (ISI range 0–28 points). From a distribution-based perspective, *d* = 0.5 is a commonly used lower limit for the smallest difference considered important [59], which corresponds to 2.3 points on the ISI. Second, as the non-inferiority margin should be smaller than the minimal important difference, 2 points on the ISI are an upper limit for the non-inferiority margin. Contrary to the minimal important difference, the non-inferiority margin should describe a clinically negligible difference. We agreed that the boundary between “minimal important” and “clinically negligible” is not sharply delineated, meaning that the boundary should not be set directly; for example, 0.1 points below the clinically relevant difference. There was no doubt that a 1-point difference is a clinically negligible difference. From a distribution-based perspective, 0.9 points correspond to a *d* = 0.2 (small) effect size according to Cohen’s taxonomy. Third, integrating these different perspectives, clinical and statistical arguments, with clinical reasoning being more important to us, a group difference δ of 1.5 points was conservatively considered clinically negligible and hence chosen as the non-inferiority margin. We intend to demonstrate non-inferiority of therapist-guided iCBT-I versus face-to-face CBT-I with regard to post-intervention ISI scores based on a shifted *t*-test at a one-sided significance level of 2.5%. To test for non-inferiority, the null hypothesis that ISI scores in the face-to-face CBT-I arm are ≥ 1.5 points higher than in the therapist-guided iCBT-I arm with an assumed common standard deviation of 4.5 points is rejected if the two-sided 95% confidence interval (CI) for the difference in ISI scores (control versus experimental) is < 1.5 points. To achieve 90% power, 382 patients must be included in analysis (191 per group; nQuery Advisor 7.0). Non-compliance and drop-out after randomisation are assumed to be no more than 10% [37]. Therefore, 422 patients will be randomised.

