## Statistical methods

### Statistical methods for primary and secondary outcomes {20a}

#### Efficacy

The primary efficacy analysis will be performed in the per-protocol set, excluding patients with major protocol violations since it is generally recognised that “in an equivalence or non-inferiority trial, use of the full analysis set is generally not conservative” (European Medicines Agency—CPMP/ICH/363/96, Sect. 5.2.3, p. 26). For sensitivity analysis, the same analysis will be performed according to the intention-to-treat principle, based on the full analysis set, including all randomised patients with their original treatment allocation. The effects of internet-delivered and face-to-face CBT-I—with respect to the primary endpoint ISI at post-intervention—will be tested within a linear mixed model for repeated measures with corresponding two-sided 95% confidence intervals (CIs). The model will include treatment and study centre as independent variables. In cases involving low recruitment rates at specific centres, additional sensitivity analyses will be performed. The one-sided test of non-inferiority (internet-delivered versus face-to-face CBT-I) at a significance level of 2.5% will be based on the two-sided 95% CI from the mixed model for repeated measures. The null hypothesis will be rejected if the lower limit of the CI for the difference lies entirely above -1.5 points.

If non-inferiority is concluded, a test for superiority of therapist-guided iCBT-I versus face-to-face CBT-I will be conducted. For this, the primary analysis will be repeated in the full analysis set. If the resulting two-sided 95% CI lies entirely below zero, superiority of therapist-guided iCBT-I versus face-to-face CBT-I will be concluded. As this is a closed test procedure, it will not be necessary to adjust the significance level *α* (see “Points to consider on switching between superiority and non-inferiority” EMA—CPMP/EWP/482/99). Analysis in the mixed model for repeated measures will permit valid inferences under the “missing at random” assumption, which seems justified since we expect that most of the missing data will be absent for reasons probably unrelated to the missing outcomes. Secondary endpoints will be analysed in a fashion similar to the primary outcome, using regression models, as appropriate, for the respective type of data. Treatment effects will be calculated using two-sided 95% CI.

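### The terms listed for the primary repeated-measures model give a treatment difference averaged over visits, not the week-10 ISI difference that is the primary endpoint

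*Protocol article*

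**What the plan says.** Under Primary outcome, the protocol article states: "The primary study outcome will be insomnia severity at post-intervention, assessed using the Insomnia Severity Index". Objectives {7} places that assessment 10 weeks after randomisation. The ISI is also collected at baseline and at 6 months.

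Under Statistical methods {20a}, Efficacy, the treatment effects "with respect to the primary endpoint ISI at post-intervention—will be tested within a linear mixed model for repeated measures". The terms follow: "The model will include treatment and study centre as independent variables". The one-sided non-inferiority test "will be based on the two-sided 95% CI from the mixed model for repeated measures". The superiority test repeats this analysis in the full analysis set.

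The section does not say which visits are responses, whether the treatment effect may differ by visit, how baseline ISI enters, or which contrast of the fitted model gives the interval.

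Sample size {14} works with a single time point. The margin is set there ("a group difference δ of 1.5 points was conservatively considered clinically negligible and hence chosen as the non-inferiority margin"), and the test is "based on a shifted *t*-test at a one-sided significance level of 2.5" per cent on post-intervention scores.

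**The concern.** A repeated-measures model needs at least two ISI assessments per patient as responses. If its fixed effects are treatment and centre only, it has one treatment coefficient, assumed constant over every visit in the response. That coefficient is a weighted average of the visit-specific differences. The endpoint is the difference at one visit.

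The gap matters because the decision compares one interval with a 1.5-point margin. If the other visits carry smaller differences, the average is pulled towards zero, and in a non-inferiority trial that makes a false claim easier. Baseline is the clearest case, since randomisation makes its expected difference zero.

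The superiority test and the full-analysis-set sensitivity analysis use the same model, so neither would expose the problem. The data analysts are not blinded (Who will be blinded {17a}), which is a further reason to fix the contrast in advance.

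**Working it through.** **Inputs from Sample size {14}:** margin 1.5, SD 4.5, one-sided 2.5%, power 90%, 191 analysed per arm.

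**Assumed, because the article gives no value:** within-patient correlation ρ = 0.5 (range 0.3 to 0.7), the month-6 difference, SD 4.5 at every visit, compound symmetry and complete data.

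**Sign used here:** iCBT-I minus face-to-face, so a positive value means iCBT-I is worse. Non-inferiority is claimed if the upper 95% limit is below 1.5.

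**Step 1. The plan's own figure.** The normal approximation gives n per arm = 2 × (1.960 + 1.282)² × (4.5/1.5)² = 189.1, rounded up to 190. The exact noncentral-t calculation gives 191 per arm (382 in total) with power 0.901. The stated 382 is reproduced for a single-time-point comparison.

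**Step 2. The intended contrast.** SE = 4.5 × √(2/191) = 0.460. With a true week-10 difference of 1.5, the chance of claiming non-inferiority is 2.5%, as it should be.

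**Step 3. The listed terms only.** With T visits as responses, each visit has weight 1/T under the assumptions above:
- coefficient = mean of the T visit-specific differences
- SE = √[(2/191) × 4.5² × (1 + (T − 1)ρ)/T]
- false non-inferiority rate = Φ[(1.5 − coefficient)/SE − 1.96]

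Three visits, differences 0, 1.5 and 1.5:
- coefficient = 3.0/3 = 1.00
- SE = √[(2/191) × 20.25 × 2/3] = 0.376
- rate = Φ(0.50/0.376 − 1.96) = Φ(−0.63) = 26%

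Two visits, differences 1.5 and 0.75:
- coefficient = 2.25/2 = 1.125
- SE = √[(2/191) × 20.25 × 1.5/2] = 0.399
- rate = Φ(0.375/0.399 − 1.96) = Φ(−1.02) = 15%

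All cases have a true week-10 difference of 1.5:

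| Responses | Month-6 difference | Coefficient | Rate, ρ = 0.5 | Range, ρ 0.3 to 0.7 |
|---|---|---|---|---|
| Baseline, week 10, month 6 | 1.5 | 1.00 | 26% | 23 to 32% |
| Baseline, week 10, month 6 | 3.0 | 1.50 | 2.5% | 2.5% |
| Week 10, month 6 | 0.75 | 1.13 | 15% | 14 to 17% |
| Week 10, month 6 | 1.5 | 1.50 | 2.5% | 2.5% |
| Week 10, month 6 | 2.25 | 1.88 | 0.2% | 0.1 to 0.2% |

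**Step 4. When the direction changes.** With three visits, the coefficient reaches 1.5 only if (0 + 1.5 + d)/3 = 1.5, so d = 3.0, twice the week-10 difference. Below that, the average favours non-inferiority. With two post-baseline visits, the turning point is equality of the two differences.

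**Step 5. Simulation check.** With 2,000 trials per scenario, ρ = 0.5 and no centre term, an unstructured covariance and an equal-weight analysis agreed with the formulas to within simulation error. The three-visit case in the first row gave 24 to 27%, with or without an 8-point fall in mean ISI after baseline. The two-visit case with month-6 difference 0.75 gave 16%, and with equal differences about 3%.

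**The case against.** The strongest reply is that the article never says the model contains nothing else. It says what the model will include, and the sentence before ties the test to ISI at post-intervention. No section says that baseline is a response or that month 6 enters the primary comparison. A model without time would also assume no mean change after baseline, although the Discussion expects both formats to reduce insomnia severity. The natural intention is therefore a contrast at week 10, and the visit terms and covariance structure may well stand in the full protocol or an SAP, neither of which is shown.

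Much of this stands. A reader might infer that the trial will be analysed with treatment and centre alone. The article does not establish that. A reader might also infer that the analysis is biased towards non-inferiority as such. It is not: with two post-baseline visits and equal differences there is no bias, and if the difference grows the test becomes too strict.

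What does not fall away is that the article goes beyond leaving the model to another document. It lists the independent variables for the decisive test, and that list does not deliver the stated endpoint. An analyst following it as written would report a different quantity.

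**Conclusion.** The point holds as a defect in the stated specification. The listed terms yield a visit-averaged treatment difference, while the endpoint, the margin and the sample size all refer to week 10.

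The direction is conditional. If baseline is among the responses, the estimate is diluted in favour of non-inferiority unless the month-6 difference is at least twice the week-10 difference. With week 10 and month 6 only, it favours non-inferiority if the difference shrinks, is unbiased if it is constant, and works against non-inferiority if it grows.

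The rates of about 26% and 15% against a nominal 2.5% are what-if figures. They rest on an assumed correlation and assumed month-6 differences, on equal visit weights and on a literal reading of the term list. They show how much the unstated choices could matter; they do not predict this trial's error rate.

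**What to change.** In Statistical methods {20a}, Efficacy, state the primary model as post-baseline ISI (week 10 and month 6) on treatment, visit, treatment-by-visit, study centre and baseline ISI. State that both the non-inferiority and the superiority confidence intervals come from the treatment contrast at week 10 only. The covariance structure and any baseline-by-visit term can be left to the SAP.

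The cost is a change of wording and three further fixed-effect parameters (visit, treatment-by-visit, baseline ISI) with about 380 patients analysed. The sample size of 382 analysed is unaffected, because it was planned for one time point. Baseline ISI is already collected. Under the assumed correlation of 0.5, adjusting for it would lower the week-10 SE from 0.46 to about 0.46 × √(1 − 0.5²) = 0.40.

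If the full protocol or the SAP already names these terms and this contrast, only the article's text needs to be reconciled with it.

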### Objectives {7}

This trial’s primary objective is to investigate the non-inferiority of therapist-guided iCBT-I versus face-to-face CBT-I using the primary endpoint, the Insomnia Severity Index (ISI; [27]) after treatment completion (10 weeks after randomisation). This will be investigated in an adequately powered sample in routine clinical care, ensuring the same therapeutic content and same therapist qualification level in both interventions. It is hypothesised that therapist-guided iCBT-I is non-inferior to individual face-to-face CBT-I. Secondary objectives of this trial are: (1) to perform a health-economic evaluation of the two interventions and (2) to systematically explore potential benefits and disadvantages associated with iCBT-I.

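### The non-inferiority rule bounds the wrong side of the confidence interval, and no sign convention makes the protocol's three direction statements correct together

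*Protocol article*

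**What the plan says.** The aim is set in Objectives {7}: "It is hypothesised that therapist-guided iCBT-I is non-inferior to individual face-to-face CBT-I". The endpoint is the ISI total after treatment, with "response options ranging from 0 to 4 and a total score ranging from 0 to 28" (Primary outcome). It measures insomnia severity. The Introduction treats a larger reduction as an advantage and the Discussion describes the expected benefit as a reduction, so higher is worse.

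Three statements then give the direction of the comparison.

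1. **Sample size {14}.** The margin is set as follows: "a group difference δ of 1.5 points was conservatively considered clinically negligible and hence chosen as the non-inferiority margin". The null hypothesis is that face-to-face ISI scores are at least "1.5 points higher than in the therapist-guided iCBT-I arm". It is rejected if the two-sided 95% CI "for the difference in ISI scores (control versus experimental) is" less than 1.5 points.
2. **Efficacy {20a}, non-inferiority.** The test is labelled with the internet arm first and face-to-face second. The rule is: "The null hypothesis will be rejected if the lower limit of the CI for the difference lies entirely above -1.5 points".
3. **Efficacy {20a}, superiority.** After non-inferiority, the same model is refitted to the full analysis set, with this criterion: "If the resulting two-sided 95% CI lies entirely below zero, superiority of therapist-guided iCBT-I versus face-to-face CBT-I will be concluded".

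**The concern.** On a scale where higher is worse, an inferior iCBT-I gives a positive difference when face-to-face is subtracted from iCBT-I. Non-inferiority then depends on the upper confidence limit. The protocol puts its condition on the lower limit, while its superiority rule makes sense only for that same order of subtraction. The null in the Sample size section describes iCBT-I as better, so rejecting it would support non-inferiority of face-to-face to iCBT-I, which is the reverse of the stated hypothesis.

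This is the decision rule for the primary endpoint, and it is also the gate to the superiority test. Applied literally, it can pass an inferior treatment and fail a better one. The protocol also states that the data analysts are not blinded, so a sign left to be settled at the analysis stage weakens the pre-specification of the primary conclusion.

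**Working it through.** **Inputs.** All come from Sample size {14}: margin 1.5, common SD 4.5, one-sided 2.5% (two-sided 95% CI), 90% power, 191 analysed per arm. Write E for the iCBT-I mean, C for the face-to-face mean, and D = E - C, so that positive D means iCBT-I is worse.

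**The plan's own figure.** The normal formula is n per arm = 2 × (1.960 + 1.282)² × 4.5² / 1.5² = 189.1, hence 190. With the noncentral t distribution, power is 89.99% at 190 and 90.13% at 191 per arm. The stated 191 per arm (382) is therefore reproduced for a true difference of 0. The calculation is symmetric in the sign, so it does not reveal the error.

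**Each statement under each sign.** Non-inferiority of iCBT-I means E - C < 1.5, or equivalently C - E > -1.5.

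| Statement | If the difference is E - C | If the difference is C - E |
|---|---|---|
| Sample size: null in words (C at least 1.5 above E) | wrong (arms are named) | wrong (arms are named) |
| Sample size: CI below 1.5 | right, but against its own label | wrong |
| Efficacy: lower limit above -1.5 | wrong | right |
| Efficacy: superiority if CI below 0 | right | wrong |

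Neither column is right throughout. If each section's label is read as an order of subtraction, the two non-inferiority rules become C - E < 1.5 and E - C > -1.5. These are the same inequality, and both guard against the wrong error.

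**Size of the effect, with the difference taken as E - C.**

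- SE = 4.5 × √(2/191) = 0.460. The CI half-width is 0.905 (t on 380 df).
- Written rule: non-inferiority is declared if the observed D > -1.5 + 0.905 = -0.595. Its probability is Φ((D + 1.5 - 0.905)/0.460).
- Correct rule: observed D < 1.5 - 0.905 = 0.595. Its probability is Φ((1.5 - 0.905 - D)/0.460).

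| True D (positive = iCBT-I worse) | Written rule | Correct rule |
|---|---|---|
| -3 | about 0% | about 100% |
| -2 | 0.1% | about 100% |
| -1.5 | 2.5% | about 100% |
| 0 | 90.2% | 90.2% |
| +1.5 | 99.9997% | 2.5% |
| +2 | about 100% | 0.1% |
| +3 | about 100% | about 0% |

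**Effect on the superiority test.** On D, superiority needs an observed value below -0.905, while the written non-inferiority rule needs one above -0.595. Put another way, the interval is about 1.81 points wide and cannot fit between -1.5 and 0. On one and the same estimate the two written rules cannot both be met, so the sequence cannot reach superiority.

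**The case against.** The best defence is that the Efficacy section never writes a subtraction. Naming the internet arm first may only name the comparison, and the one explicit direction for an ISI difference is in Sample size {14}, with control first. Read as face-to-face minus iCBT-I, the quoted -1.5 rule is correct, and the error rates above do not apply to it. The intent is also clear from the objectives and from the discussion of the margin, and a competent statistician would probably implement it correctly. Sample size, margin and alpha are untouched.

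Much of this is fair. The near-100% figures belong to the iCBT-I-minus-face-to-face reading and should be quoted with that condition. The defence does not remove the error, however. Under face-to-face minus iCBT-I, an interval entirely below zero means that iCBT-I is worse, and the protocol would label that superiority. At the planned precision the gate would block that false claim on a single estimate, since it too needs an interval of about 1.81 points to fit between -1.5 and 0, but genuine superiority could then never be declared either. The rejection rule in the Sample size section would also be wrong, and its null in words stays reversed because it names the arms. No other section corrects any of this. A statistical analysis plan, which is not shown, might state the rule properly, but the contradiction in the protocol would remain.

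**Conclusion.** The concern holds. The superiority rule, stated for a repeat of the primary analysis, fixes the difference as iCBT-I minus face-to-face, and on that scale the written non-inferiority rule bounds the wrong side. It would declare non-inferiority almost certainly when iCBT-I is 1.5 points or more worse, where the intended error is at most 2.5%, and would succeed only 2.5% of the time when iCBT-I is 1.5 points better. The probabilities of the two rules coincide only at a true difference of 0 (about 90%).

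The figures assume SD 4.5, 191 analysed per arm, a normal approximation, and a mixed-model SE close to that of the planned *t*-test. A smaller SE would not cure the direction of the rule. The incompatibility with the superiority rule would ease only if the interval were narrower than 1.5 points, that is with an SE below about 0.75/1.966 = 0.38. It also supposes similar per-protocol and full-analysis-set estimates. The contradiction between the three statements needs no numerical assumption. The rule has to be corrected before analysis.

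**What to change.** Define the difference once, as mean ISI in the iCBT-I arm minus mean ISI in the face-to-face arm, with positive values meaning iCBT-I is worse, and use it throughout:

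- **Sample size {14}:** the null hypothesis is that iCBT-I minus face-to-face is at least +1.5. It is rejected if the upper limit of the two-sided 95% CI is below +1.5. Replace the reversed null and the control-first label.
- **Efficacy {20a}, non-inferiority:** concluded if the upper limit of the two-sided 95% CI is below +1.5. Delete the condition on the lower limit and -1.5.
- **Efficacy {20a}, superiority:** concluded if the upper limit in the full analysis set is below 0. This agrees with the present wording once the difference is defined.

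With this rule the probability of declaring non-inferiority is 2.5% at a true difference of +1.5 and 90.2% at 0. The cost is a short amendment to wording, plus a check that any statistical analysis plan uses the same definition. Data collection, the margin, the sample size of 382 analysed, and power are unchanged.

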#### Economic evaluation

The health-economic evaluation will be performed from a societal and a public healthcare perspective with a time horizon of 6 months. In the full analysis set, we will employ two multilevel models, one to assess costs and the other to examine effects, taking into account the data’s hierarchical structure. For effects, normal-based 95% CIs will be estimated whereas for costs, 95% CIs will be estimated using bias-corrected and accelerated bootstrapping with 5000 replications [61]. Multilevel models will be combined with cluster bootstrapping [62], wherein entire clusters rather than individual data points will be resampled, thereby preserving the hierarchical data structure. The bootstrapped cost and effect pairs will be presented on both (a) a cost-effectiveness plane and (b) a cost-effective acceptability curve disclosing the probability that therapist-guided iCBT-I is cost-effective for a wide range of willingness-to-pay thresholds [63]. When the health outcomes produced are empirically proven to be equivalent, a cost-minimization analysis (CMA) will be deemed an appropriate methodology [64]. Sensitivity analyses will be performed to assess the impact of the varying input parameters used in the analyses.

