**Methods:**

This study protocol describes a randomised controlled two-arm parallel-group non-inferiority trial comparing therapist-guided iCBT-I with face-to-face CBT-I in routine clinical care. A total of 422 patients with insomnia disorder will be randomised and treated at 16 study centres throughout Germany. Outcomes will be assessed at baseline, 10 weeks after randomisation (post), and 6 months after randomisation (follow-up). The primary outcome is insomnia severity measured using the Insomnia Severity Index. Secondary outcomes include depression-related symptoms, quality of life, fatigue, physical activity, daylight exposure, adverse events related to treatment, and a health-economic evaluation. Finally, potential moderator variables and several descriptive and exploratory outcomes will be assessed (e.g. benefits and disadvantages of internet-delivered treatment).

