## Assignment of interventions: allocation

### Sequence generation {16a}

Patients will be randomised to one of the two treatment arms with a 1:1 allocation ratio. Treatment allocation will be done centrally in the eCRF in REDCap® by the Clinical Trials Center (CTU) of the Medical Center—University of Freiburg. For each study centre, block randomisation with varying block sizes will be performed, with all group allocations concealed from the investigators to minimise selection bias.

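### If the 16 centres are the resampled clusters, the planned BCa cost intervals cover about 90–92% rather than 95%; the cluster level is not named and needs a few-cluster correction

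*Protocol article*

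**What the plan says.** The Economic evaluation section of the protocol article plans "two multilevel models, one to assess costs and the other to examine effects", in the full analysis set and over six months. These are combined with a cluster bootstrap "wherein entire clusters rather than individual data points will be resampled". For costs, "95% CIs will be estimated using bias-corrected and accelerated bootstrapping with 5000 replications". Effects are treated differently: "For effects, normal-based 95% CIs will be estimated". The bootstrapped cost and effect pairs then feed the cost-effectiveness plane and the acceptability curve.

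The section refers to a hierarchy in the data but does not name its levels. Elsewhere, the abstract says that patients are "randomised and treated at 16 study centres throughout Germany", and Sample size {14} says "Therefore, 422 patients will be randomised". Sequence generation {16a} says "For each study centre, block randomisation with varying block sizes will be performed", so both arms occur in every centre. The intervention description has every therapist treating in both arms but does not say how many therapists there are.

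**The concern.** A bootstrap that resamples whole clusters has only as many independent units as there are clusters. With few clusters, a percentile or BCa interval falls short for two reasons. The bootstrap variance lacks the factor K/(K−1), and the limits behave like normal quantiles rather than t quantiles on K−1 degrees of freedom. Going to 5000 replications removes Monte Carlo noise but adds no clusters. BCa adjusts for bias and skewness, not for the number of clusters.

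The health-economic evaluation is the first of the two secondary objectives, and the discussion presents it as evidence for policymakers. Intervals that are too narrow would make the cost difference look more certain than the data allow. On the acceptability curve, probabilities would be pushed towards 0 or 1.

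**Working it through.** The plan states a nominal 95% level and no achieved coverage, so there is no coverage figure of its own to reproduce.

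**Inputs from the protocol article:** 16 centres (abstract); 422 randomised (Sample size {14}), so 422/16 ≈ 26 per centre if sizes are equal; both arms in each centre (Sequence generation {16a}); BCa limits for costs and whole-cluster resampling (Economic evaluation).

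**Assumptions not in the article:** cluster = centre in the main case; intraclass correlation 0.05; coefficient of variation of cluster size 0 or 0.6; SD of the treatment effect between centres 0 or 0.2 outcome SD; outcomes normal or lognormal (sigma 1); 40 or 60 clusters for the therapist reading.

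**Step 1, theory for K equal clusters.** Coverage = P(|t(K−1)| < 1.96 × √((K−1)/K)).
- K = 16: 1.96 × √(15/16) = 1.898, and P(|t(15)| < 1.898) = 0.923.
- K = 30: 0.936. K = 50: 0.942.

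**Step 2, size of the correction.**
- Widening needed at K = 16: √(16/15) × 2.131/1.960 = 1.033 × 1.087 ≈ 1.12.
- The uncorrected interval is therefore 1 − 1/1.12 ≈ 11% too narrow.

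**Step 3, simulation.** 3000 trials per scenario, 1000 cluster resamples each, N = 422, within-cluster treatment contrast. The Monte Carlo standard error is about 0.5 points. Coverage of nominal 95% intervals:

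| Clusters | Outcome | Percentile | BCa | t(K−1) on cluster-jackknife SE |
|---|---|---|---|---|
| 16 | normal | 91.1–91.9% | 91.0–92.0% | 94.3–95.1% |
| 16 | skewed | 91.1–91.7% | 90.1–90.4% | 94.6–95.6% |
| 40 or 60 | normal | 93.7–94.6% | 93.5–94.6% | 94.8–95.6% |
| 40 or 60 | skewed | 92.6–93.1% | 90.6–91.9% | 94.5–95.4% |

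Rows for 16 clusters cover between-centre effect SDs of 0 and 0.2. The shortfall is much the same at both, so it does not depend on centre-by-treatment variation. Rows for 40 or 60 clusters use SD 0 only.

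A repeat of the 16-cluster scenarios gave BCa coverage of 91.9–92.4% (normal) and 89.9–90.3% (skewed).

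**Step 4, does a correction work?** Scaling percentile deviations by 1.12 gave 94.3–94.9% in all eight 16-cluster scenarios. Scaling the BCa limits themselves reached only 93.3–93.4% on skewed data.

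**The case against.** The strongest objection is that the section never says that clusters are centres. Therapists are a possible level. So are patients with repeated measurements, since costs are assessed twice and quality of life three times. With 422 patients as clusters, the Step 1 formula gives 94.9% and there is no defect. It stands that the 90–92% depends on the reading. The centre is still the most natural one: it is the randomisation stratum, a term in the primary model, and the only such unit that the article counts. The patient reading fits less well, because healthcare costs are computed per participant and QALYs are one area under the curve per patient. It cannot be excluded from the text.

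Second, not all of the shortfall comes from having few clusters. At K = 40 the factor needed is only √(40/39) × 2.023/1.960 ≈ 1.05, yet BCa coverage on skewed costs stays near 92%. That stands: part of the loss is BCa itself on skewed data. It argues against BCa here rather than for it.

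Third, an unseen analysis plan might add a correction. That is possible. But the article does fix the interval type and the resampling unit, and this combination causes the shortfall.

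A reader might also infer that every 95% interval in the trial is affected. The documents do not support this. BCa is specified for costs only, and the source of the standard error for the normal-based effect intervals is not stated. The primary non-inferiority test uses a separate mixed model and no bootstrap is planned for it.

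**Conclusion.** The point holds in conditional form. If the 16 centres are the clusters, the nominal 95% BCa cost intervals cover about 90–92%, a loss of 3–5 points. They are about 11% too narrow. The plane and the acceptability curve share the same replicates and understate uncertainty as well. With an assumed 40–60 therapists, the loss is small for normal outcomes (about 0.5–1.5 points) but remains about 3–4.5 points for skewed costs.

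The figures rest on the assumed correlation, size variation and skewness listed above, and on a centre-adjusted mean difference in place of the planned multilevel model, whose levels are not given. The issue is confined to a secondary objective. The article attaches no hypothesis test to the cost intervals, so the point should be corrected but does not threaten the trial's main conclusion.

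**What to change.** Name the centre as the resampled cluster. Replace the uncorrected BCa interval for costs with one of these:
- percentile limits whose deviations from the estimate are multiplied by √(K/(K−1)) × t(K−1)/z, about 1.12 for K = 16;
- a t(K−1) interval on a cluster-jackknife standard error;
- a bootstrap-t interval, which was not simulated here.

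Apply the same scaling to the replicate deviations behind the cost-effectiveness plane and acceptability curve. The factor is set at the 95% limits, so near the middle of the curve it widens slightly more than needed.

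Resampling patients within arm is not a useful check. In simulation it covered 93–95% with no centre-by-treatment variation, but only 90–91% when that SD was 0.2.

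The cost is a few words of text and a line of code, with no change to data collection. The downside is that reported cost intervals become about 12% wider.
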